### Setting

RADAR involves collaboration with several First Nations communities in Alberta, representing separate treaty areas across the province (continuous expansion of the RADAR model to additional First Nations communities is ongoing). We estimate that approximately 1000 people with type-2 diabetes currently reside in the pilot communities. All communities involved are several hours of travel from a major urban center, where the majority of diabetes specialist care services are located. Some communities have local family physician clinics, located just off reserve that also provide care for patients with diabetes; other communities have visiting family physicians on one or more days a week; while other communities have no local physician services, although services are available in neighboring rural communities. As a result, local, on-reserve, healthcare workers are the primary service providers delivering diabetes care and general health services for these populations. Prior to implementing RADAR, all communities were familiar with the CARE platform for the management of patient care within their respective communities.

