### Data analysis

For quantitative data, all relative changes will be analyzed using the last known recorded value from the CARE platform from baseline to the end of the intervention phase. We will employ an intention-to-treat analysis, whereby all patients who are enrolled and have baseline data will be included in our primary analysis. The primary endpoint (i.e., 10% improvement in any of A1c, BP, cholesterol values from baseline or those maintaining values within 10% of baseline if at any or all three targets at baseline) will be evaluated using a conventional intention to treat analysis with logistic regression. However, if the observed intracluster correlation coefficient (ICC) is non-ignorable, we will use generalized estimating equations (GEE) that accounts for the clustered and hierarchical nature of our data [24]. Several a-priori subgroup analyses are planned for the primary endpoint. First, we will restrict analyses to patients not at target for any of the 3 primary outcome measures. Second, we will restrict analyses to those patients who were at target for each primary outcome measure (A1c, BP, cholesterol) to fully examine persistence at target over time. Additional subgroups of interest include analyses stratified by sex, and analyses stratified by age (<65 vs > =65 years). Secondary endpoints include: the proportion of clinical measures completed in accordance with guidelines (e.g., A1c, BP, cholesterol, foot and eye examination, receipt of vaccinations, smoking cessation counseling); the number of patients registered in CARE; and the proportion of patients linked to a health services provider.

We anticipate not having complete quantitative data on all endpoints of interest, given the real-world implementation of the project. Several approaches will be used for missing clinical data. First, in alignment with the intention-to-treat approach, we will use the baseline observation carried forward technique for our primary outcome. The stability of the results will be additionally evaluated using the multiple imputation method as a sensitivity analysis.

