### Power and sample size

In prior studies, about 40% of diabetes patients will have at least a 10% improvement in A1c, BP, and cholesterol over time when studied under ‘usual care’[32]. To detect at least an additional 10% improvement in the proportion of patients achieving our primary endpoint under the RADAR model (i.e., move the population from 40% achieving endpoint to at least 50% achieving endpoint), at an alpha =0.05, an ICC of 0.01, we require 1153 total patients to detect a clinically important difference with 80% power. Assuming a 10% loss to follow-up, we require approximately 1250 total patients among our communities.

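### Community clustering enters the primary analysis only if the observed ICC is judged non-ignorable; this gate is unreliable and can push the false-positive rate above 5%

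*Protocol article*

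**What the plan says.** In the protocol article, Data analysis, the primary endpoint "will be evaluated using a conventional intention to treat analysis with logistic regression". The next sentence provides for clustering only conditionally: "if the observed intracluster correlation coefficient (ICC) is non-ignorable, we will use generalized estimating equations (GEE"). No cut-off or test for this judgement is given.

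Power and sample size plans for clustering: "at an alpha =0.05, an ICC of 0.01, we require 1153 total patients". The target is to "move the population from 40% achieving endpoint to at least 50% achieving endpoint", and the total is the number needed "to detect a clinically important difference with 80% power". It then adds: "Assuming a 10% loss to follow-up, we require approximately 1250 total patients among our communities".

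Setting does not give the number of communities: "RADAR involves collaboration with several First Nations communities in Alberta". It estimates that "approximately 1000 people with type-2 diabetes currently reside in the pilot communities". Implementation and evaluation says that communities switch to RADAR one after another, each acting as its own control. The Discussion explains that neither patients nor health workers could be randomised, because the effects would spread through a whole health facility.

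**The concern.** The intervention reaches patients through their community, so outcomes within a community may be alike whatever ICC happens to be estimated. The Discussion's argument about diffusion within a facility is itself a reason to expect this. Under the stated rule, the model behind the primary p-value and confidence interval is chosen after looking at the outcome data, and the choice rests on a quantity that few communities estimate badly. When the check misses real clustering, the interval is too narrow and RADAR can be declared effective by chance more often than the stated alpha allows.

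The missing cut-off is not the point, since an analysis plan could supply one. The point is the stated rule that independence is the default and clustering must first be shown.

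**Working it through.** **Inputs.** From Power and sample size: 40% against 50%, alpha 0.05, power 80%, ICC 0.01, 1153 patients, about 1250 after losses. Assumed: a two-sided test, equal communities, and 6 to 24 communities.

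**1. The plan's own figure.** Without clustering, n per group = [1.96·√(2·0.45·0.55) + 0.842·√(0.40·0.60 + 0.50·0.50)]² / 0.10² = 387.3, so 388 per group and 776 in total. 1153/776 = 1.49. Setting 1 + (m − 1)·0.01 = 1.49 gives m = 50 patients per community, and 776 × 1.49 = 1156, close to 1153. At 50 each, 1153 patients come from about 23 communities. This is back-solved, because the article states neither the cluster size nor the number of communities.

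**2. Error if clustering is ignored.** For a between-community comparison, the design effect is DE = 1 + (m − 1)·0.01 and the actual error is 2·[1 − Φ(1.96/√DE)].

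**3. How often the check fails.** With J communities split between two conditions, the F ratio behaves approximately as [1 + m·0.01/0.99] times an F variable on J − 2 and N − J degrees of freedom. The miss rate is the probability that this falls below the 5% critical value. For J = 6, m = 208, the factor is 3.10, the critical value is 2.38, and P(F < 2.38/3.10) = 45%.

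**4. Error of the two-step rule.** Beta-binomial simulation with a 40% rate, no true effect, 1250 patients and 40,000 trials per row. The adjusted branch is a valid community-level t-test, so that only the gate is at fault.

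| Communities | Patients each | DE | Unadjusted error | F-test misses ICC | Two-step error | Always adjusting |
|---|---|---|---|---|---|---|
| 6 | 208 | 3.07 | 26% | 45% | 12% | 5% |
| 8 | 156 | 2.55 | 22% | 44% | 10% | 5% |
| 12 | 104 | 2.03 | 17% | 46% | 9% | 5% |
| 24 | 52 | 1.51 | 11% | 56% | 7% | 5% |

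A one-sample comparison with a fixed 40% gives miss rates of 39 to 55% and similar two-step errors. With 1000 patients, the Setting estimate, the two-step error is again 7 to 12%, and the F-test misses 53 to 66%.

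**5. Dependence on the threshold.** If any observed ICC above 0 triggers the valid community-level analysis, the error stays at about 4.7 to 5.3%. If the cut-off is an ICC of 0.02, it is about 22%, 19%, 15% and 10% for 6, 8, 12 and 24 communities.

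**6. Dependence on the contrast.** Simulated staggered layouts at ICC 0.01 gave an unadjusted error of 6.5 to 9.7% with 24 communities and 7.5 to 15.6% with 10. The range covers different patients per period, analyses with and without period terms, and community effects that were stable or drifted over time.

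The result differs if the same patients are compared between phases and community levels are stable. The community effect then cancels, and unadjusted logistic regression ignores the within-patient correlation r. Its error is about 2·[1 − Φ(1.96/√(1 − r))]: 3.9% at r = 0.1, 2.3% at r = 0.26 and 0.6% at r = 0.5. The article gives no r, so these values are assumptions. With r about 0.26 and 1200 patients, the two-step rule gives:

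| Share of the ICC that is community-by-phase | 6 communities | 12 | 24 |
|---|---|---|---|
| None | 4.5% | 4.9% | 4.8% |
| 20% | 5.1% | 4.9% | 4.9% |
| 50% | 7.3% | 5.4% | 4.4% |
| 100% | 12.6% | 8.1% | 5.5% |

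**The case against.** The strongest reply is that the design is within-community. Each community is its own control and the endpoint is a change from baseline, so a between-community simulation does not describe the contrast. This stands in part. For a balanced before-after comparison of the same patients with stable community levels, the rule does not inflate the error, and the unadjusted model is conservative. Material inflation there needs few communities and about half or more of the ICC to be specific to the phase. The reply is not complete, because the roll-out is staggered and the unadjusted error exceeds 5% in staggered layouts.

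A second reply is that the threshold and the number of communities are the reviewer's assumptions. That is correct. A low threshold with a small-sample-valid analysis would hold the error near 5%, and the only community size recoverable from the plan, about 50, gives the mildest result in the table. The article does not commit to such a threshold, however, and no reading of the rule does better than always adjusting.

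A third reply is that enlarging the sample for an ICC of 0.01 is a prudent provision in case the GEE branch is needed. That also stands. A reader might infer that the sample-size section contradicts the analysis section. The two are in tension, since the trial is enlarged by half for a feature that the default analysis leaves out, but they can both be followed.

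**Conclusion.** The point holds as a weakness of the stated rule, with a size that is conditional. Gating the treatment of clustering on the observed ICC is unreliable at the plan's own ICC of 0.01. In a between-community comparison of 1250 patients with a 5% F-test as gate, the false-positive rate is about 7% near 23 to 24 communities and about 9 to 12% with 6 to 12. The number of communities, the gate and the contrast behind these figures are assumptions.

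A reader might go further and conclude that the trial's error certainly exceeds 5%, or that it reaches the 11 to 26% of a wholly unadjusted analysis. The documents do not support that. They do not fix the number of communities, the threshold or the exact contrast, and under some admissible choices there is no inflation. The rule should be fixed because the primary inference depends on it and the better alternative is simple.

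**What to change.** In Data analysis, delete the condition on the observed ICC. State that the primary analysis always accounts for community, and for repeated scores of the same patient where both phases are scored. Name in advance a method suited to the number of communities, such as a mixed or GEE model with a small-sample correction, or a community-level paired analysis. The correction matters: in the two-arm simulation with 1153 patients, always using GEE with an uncorrected robust standard error still gave 7.3% with 24 communities and 18.4% with 6. Report the ICC with its interval as a descriptive result only.

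The cost is a sentence or two and no new data. Intervals become wider where clustering is real. For a between-community contrast at ICC 0.01, the factor is √DE, about 1.2 at 50 patients per community (√1.49) and 1.75 at 208 (√3.07), before any allowance for few degrees of freedom. For a within-community contrast with stable levels, accounting for the repeated scores may make them narrower.

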### Outcomes

The primary outcome will be a 10% improvement in measures over the baseline control periods in any one of the following: A1c, BP, cholesterol. This is consistent with our previous Canadian work that considers a 10% improvement in any of these measures to be the minimally clinically important difference [20]. For patients who are already at ‘target’ for any or all three measures at baseline, we will consider persistence at target (i.e., maintain values within 10% of baseline) as also achieving the primary outcome. Secondary endpoints will address other areas of diabetes care and process indicators compared to baseline including: the proportion of clinical measures and tasks completed in accordance with Canadian Diabetes Association Clinical Practice guidelines (e.g., A1c, BP, cholesterol, foot and eye examination, receipt of vaccinations, smoking cessation counseling); the number of patients registered in CARE; and the proportion of patients linked to a health services provider. In addition, we are collecting detailed information to conduct a comprehensive economic evaluation, assessing the cost-effectiveness of RADAR specific to these communities. Our approach to the economic analysis will be analogous to methods previously published by our group [21, 22].

We will also conduct a qualitative assessment as part of our comprehensive evaluation to supplement the primary and secondary quantitative assessments. The purpose of the qualitative component is to provide contextual information, such as the quality/usability of the CARE platform and the impact/satisfaction of local healthcare workers with the CC model.

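### Baseline carried forward settles the primary outcome of patients without follow-up by baseline status alone: success if at target, failure if not

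*Protocol article*

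**What the plan says.** Four rules in the protocol article meet here.

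- **Endpoint (Outcomes).** Success is a 10% improvement in any one of A1c, BP or cholesterol. For patients already at target, "we will consider persistence at target (i.e., maintain values within 10% of baseline) as also achieving the primary outcome". The Data analysis section repeats this for "those maintaining values within 10% of baseline if at any or all three targets at baseline".
- **Analysis set (Data analysis).** "all patients who are enrolled and have baseline data will be included in our primary analysis". A follow-up value is not required.
- **Value analysed (Data analysis).** Change is assessed "using the last known recorded value from the CARE platform from baseline to the end of the intervention phase".
- **Missing data (Data analysis).** The article says "We anticipate not having complete quantitative data on all endpoints of interest". Its first approach is baseline observation carried forward (BOCF), adopted "in alignment with the intention-to-treat approach": "we will use the baseline observation carried forward technique for our primary outcome". Multiple imputation is planned as a sensitivity analysis only.

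Two planned subgroups matter. One takes patients at none of the three targets. The other will "restrict analyses to those patients who were at target for each primary outcome measure", in order to study persistence.

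**The concern.** BOCF is workable for an endpoint that requires change, because no change then means no success. This endpoint has a second route, in which no change is the success. Under that route the missing-data rule supplies the evidence of success itself.

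The primary outcome of a patient without follow-up then carries no information about what happened to that patient. It only restates whether the patient was at target at baseline. The intervention works through monitoring and recall, so an at-target patient who is never recalled and re-measured should not be recorded as having persisted. The problem is sharpest in the at-target subgroup, whose purpose is to measure persistence: there, every patient with no follow-up value persists by construction.

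**Working it through.** **Mechanism.** The carried-forward value equals baseline, so the relative change is baseline/baseline - 1 = 0%.

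- At target at baseline: 0% is within 10%, so success.
- At no target: 0% is not a 10% improvement, so failure.

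This holds whether the any-or-all-three wording requires one at-target measure to be maintained or every at-target measure, because all of them are carried forward. If one is enough, a patient at target on cholesterol only, with no repeat cholesterol, also succeeds automatically even when A1c and BP were re-measured and had worsened.

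**Inputs.** The article gives no figure for the effect of BOCF, so there is none to reproduce. The sample size of 1153 is not an input.

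- d, share with no follow-up value: 10%, borrowed from the loss to follow-up in Power and sample size.
- s, true success among missing off-target patients: 40%, borrowed from the usual-care rate in the same section. Applying it to this group is an assumption.
- a, at-target share among the missing: not in the article; 30% to 90% assumed.
- r, true persistence among missing at-target patients: not in the article; 50% to 90% assumed.

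**At-target subgroup.** BOCF scores 100% of the missing as successes where the truth is r, so the bias is d(1 - r), which is never negative.

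- r = 80%: 0.10 × 0.20 = +2 points.
- r = 50%: 0.10 × 0.50 = +5 points.

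**Whole sample.** Missing at-target patients are over-scored by (1 - r), and missing off-target patients are under-scored by s:

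net shift = d × [a(1 - r) - (1 - a)s]

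In percentage points, with d = 10% and s = 40%:

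| a | r = 50% | r = 70% | r = 90% |
|---|---|---|---|
| 30% | -1.3 | -1.9 | -2.5 |
| 50% | +0.5 | -0.5 | -1.5 |
| 70% | +2.3 | +0.9 | -0.5 |
| 90% | +4.1 | +2.3 | +0.5 |

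The extremes are 0.10 × (0.30 × 0.10 - 0.70 × 0.40) = -0.025 and 0.10 × (0.90 × 0.50 - 0.10 × 0.40) = +0.041.

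**Break-even.** The shift is zero at a = s/(s + 1 - r):

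- r = 50%: 0.4/0.9 = 44%
- r = 70%: 0.4/0.7 = 57%
- r = 80%: 0.4/0.6 = 67%
- r = 90%: 0.4/0.5 = 80%

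Above these shares BOCF inflates the success rate; below them it deflates it. High shares are possible because one target is enough. If 20%, 30% or 40% met each target independently (assumed), 1 - (1 - p)³ gives 49%, 66% or 78% at one or more.

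**Dependence on the rule.** Scoring missing as not achieved lowers the overall rate by d × a relative to BOCF: 3, 5, 7 or 9 points for a = 30%, 50%, 70% or 90%.

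**The case against.** **Existing safeguards.** The article already plans multiple imputation as a sensitivity analysis, and a subgroup at none of the targets, where the persistence route cannot operate. Both could expose a material distortion, and that stands. Neither corrects the primary result, and neither repairs the at-target subgroup.

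**BOCF as a conservative choice that backfired.** A reader might infer this. The article does not call BOCF conservative; it links it only to intention-to-treat.

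**BOCF inflates the primary endpoint and favours RADAR.** A reader might infer this too. It is certain only for at-target patients. Missing off-target patients are all scored as failures, which pulls the other way, and the article gives neither the at-target share nor the persistence rate needed to net the two. More missing data enlarges the shift but does not fix its sign.

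**BOCF could produce the planned 50% with no effect.** With 20% missing, 87.5% of the missing at target and 40% success among those observed, 0.8 × 0.40 + 0.2 × 0.875 = 49.5%. This is not a fair case. It doubles the stated 10% loss, and it takes a 40% rate that the article describes only as improvement and applies it to an endpoint that also counts persistence. If off-target patients succeed at 40%, at-target patients would also have to succeed at only 40%, despite their extra route. With s = 40% and r = 80%, the shift at 20% missing and 87.5% at target is 0.2 × (0.875 × 0.2 - 0.125 × 0.4) = +2.5 points.

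**Missing as not achieved is also biased.** True: it fails stable at-target patients who were simply not re-measured. That is why it belongs in a sensitivity analysis.

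**Conclusion.** The defect follows from the article's own rules and needs no outside figure: for a patient without follow-up, baseline target status alone decides the primary outcome. In the at-target subgroup the bias is upward or zero, +2 to +5 points at 10% missing for assumed persistence of 80% to 50%.

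In the whole sample BOCF can inflate or deflate. The net shift is about -2.5 to +4.1 points at 10% missing, against a planned difference of 10 points. It is upward when the at-target share among the missing exceeds about 44% (persistence 50%) to 80% (persistence 90%).

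These sizes rest on assumed at-target shares and persistence, on 40% true success among missing off-target patients, and on reading the 10% loss as the share with no follow-up value. They are shifts in a success proportion. The 10-point difference gives scale only; the calculation does not estimate bias in a treatment contrast.

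**What to change.** In the Data analysis section:

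1. Make multiple imputation of the A1c, BP and cholesterol values the primary analysis. Impute the values and derive success or failure afterwards, so that a missing at-target patient can persist or not.
2. Report missing as not achieved as a sensitivity analysis.
3. In the at-target subgroup, state that a carried-forward baseline value never counts as persistence.

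The imputation is already planned, so the change mainly swaps roles in the text. The cost is a little more analysis work and possibly a lower reported success rate.

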### Power and sample size

In prior studies, about 40% of diabetes patients will have at least a 10% improvement in A1c, BP, and cholesterol over time when studied under ‘usual care’[32]. To detect at least an additional 10% improvement in the proportion of patients achieving our primary endpoint under the RADAR model (i.e., move the population from 40% achieving endpoint to at least 50% achieving endpoint), at an alpha =0.05, an ICC of 0.01, we require 1153 total patients to detect a clinically important difference with 80% power. Assuming a 10% loss to follow-up, we require approximately 1250 total patients among our communities.

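### The 40% usual-care rate behind the sample size is described as improvement only, but the primary endpoint also counts persistence at target, so 1153 patients and 80% power are not shown to apply to it

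*Protocol article*

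**What the plan says.** The Power and sample size section of the protocol article starts from prior studies: "about 40% of diabetes patients will have at least a 10% improvement in A1c, BP, and cholesterol over time when studied under" usual care. Persistence at target is not part of that description. The same section then sets the aim: "To detect at least an additional 10% improvement in the proportion of patients achieving our primary endpoint under the RADAR model", that is, to "move the population from 40% achieving endpoint to at least 50% achieving endpoint". With "at an alpha =0.05, an ICC of 0.01", it concludes that "we require 1153 total patients to detect a clinically important difference with 80% power".

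The endpoint itself is wider. The Outcomes section requires a 10% improvement in any one of A1c, BP or cholesterol, and adds that for patients already at target on any or all of the three, "we will consider persistence at target (i.e., maintain values within 10% of baseline) as also achieving the primary outcome". The Data analysis section repeats this as one binary endpoint: "10% improvement in any of A1c, BP, cholesterol values from baseline or those maintaining values within 10% of baseline", the second part applying to patients at target at baseline. The same section fills missing primary-outcome data by carrying the baseline observation forward.

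**The concern.** The power calculation uses one number for two quantities. The 40% is introduced as the proportion who improve by 10%, and one sentence later it is the proportion who reach the primary endpoint. The endpoint has a second route to success that the description of the 40% does not mention.

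The missing-data rule widens the gap for one group. A patient at target with no follow-up value is given the baseline value, which is within 10% of itself, and so scores as persisting.

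At stake are the sample size and the power, which readers will rely on when they interpret the primary result. The second route changes the usual-care rate. It may also change the size of the difference that RADAR can produce, because a patient who would succeed by staying stable under usual care cannot be converted into an additional success.

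**Working it through.** **Inputs from the article (Power and sample size):** 40% versus 50%; alpha 0.05 (sidedness not stated, taken as two-sided); power 80%; ICC 0.01; 1153 patients in total.

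**Inputs not in the article, so assumed:** the share *f* of patients at target on at least one measure, and the proportion *s* of them who qualify by persisting. I use *f* = 20%, 40% and 60%, with *s* = 80%.

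**Step 1: the plan's own figure.** Two-proportion formula with pooled variance, equal groups:

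n per group = [1.960·√(2p̄(1−p̄)) + 0.842·√(p₀(1−p₀) + p₁(1−p₁))]² / (p₁−p₀)²

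For 0.40 and 0.50, p̄ = 0.45: (1.960 × 0.7036 + 0.842 × 0.7000)² / 0.01 = 387.3, so 388 per group and 776 in total. The stated 1153 implies a design effect of 1153/776 = 1.486. Setting 1 + (m−1) × 0.01 = 1.486 gives a mean cluster size m of about 50. The article gives no cluster size, so this is solved backwards. I hold 1.486 fixed below, so that only the endpoint rates change.

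**Step 2: what the second route does to the rate.** Success is improvement, or persistence at target. Everyone who succeeds by improvement alone still succeeds under the wider definition. Within one population the wider rate is therefore at least the improvement-only rate. It is higher as soon as one at-target patient holds steady without improving by 10% on any measure.

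**Step 3: if a full 10-point gain survives on the wider endpoint.** Total patients, with the design effect applied:

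- 50% vs 60%: 776 × 1.486 = 1153
- 60% vs 70%: 712 × 1.486 = 1058
- 70% vs 80%: 588 × 1.486 = 874
- 80% vs 90%: 398 × 1.486 = 592

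On this reading, with a usual-care rate of 50% or more, 1153 is enough or more than enough.

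**Step 4: if RADAR acts on improvement only.** Let improvement go from 40% to 50% in all patients, and let persistence be equal in both conditions and independent of improvement. At-target patients can then succeed by either route:

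p₀ = 0.40 + 0.60·f·s and p₁ = 0.50 + 0.50·f·s, so the difference is 0.10·(1 − f·s).

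| At target (f) | f·s | Usual care | RADAR | Difference (points) | Patients needed | Power at 1153 |
|---|---|---|---|---|---|---|
| 20% | 0.16 | 49.6% | 58.0% | 8.4 | 1641 | 65% |
| 40% | 0.32 | 59.2% | 66.0% | 6.8 | 2360 | 50% |
| 60% | 0.48 | 68.8% | 74.0% | 5.2 | 3522 | 36% |

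The loss comes from the shrinking difference. The shift in the base rate alone does not cause it, as Step 3 shows.

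**The case against.** Several points on the other side have force.

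- **The source of the 40% is not shown.** It may have scored persistence as a success, and the article does call 40% the proportion achieving the endpoint. A reader might infer that the usual-care rate in this trial must exceed 40%. The documents do not support that. The ordering in Step 2 holds within one population, while the 40% comes from other studies. Carrying the baseline forward also scores a missing off-target value as no improvement, which pulls the rate down. What stands is that the article describes the 40% as improvement only and does not show that it fits the endpoint used.
- **RADAR may improve persistence too.** Suppose patients at no target go from 40% to 50% and at-target patients from 80% to 90%. With 25% at target, the rates are 0.75 × 0.40 + 0.25 × 0.80 = 50% and 0.75 × 0.50 + 0.25 × 0.90 = 60%, which needs 1153. With 50% at target they are 60% and 70%, which needs 1058. Power is then kept. This is why no direction can be asserted.
- **The wording of the three measures.** The power section joins them with an and, where the endpoint asks for any one. This is probably loose wording, and nothing here rests on it.
- **Is 40% the yardstick for success?** A reader might infer that an observed 50% to 60% would be declared a success against it. No section says so. The 40% appears only as a planning input, and the stated comparison is with each community's own control period.
- **An article condenses the full protocol.** True, but this is not an omission. The article gives a rate, describes it, and applies it to an endpoint that it defines differently.

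**Conclusion.** The mismatch stands on the article's own text: the planning rate is described as improvement only, and the endpoint is improvement or persistence. The stated 1153 patients and 80% power are therefore not shown to hold for the primary analysis.

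It would go too far to conclude that the trial is underpowered. Under the assumptions tried, power at 1153 runs from 36% (60% at target, 80% persisting in both conditions, effect on improvement only) to above 80% (a full 10-point gain kept at a base of 60% or more). Which end applies depends on three quantities that the article does not give: the share at target, the persistence rate, and any RADAR effect on persistence. All the figures also rest on a design effect solved backwards from 1153.

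This should be corrected, because the figure is relied on and the correction is cheap. The primary analysis can be run either way.

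**What to change.** State the usual-care rate and the target difference for the endpoint exactly as it will be scored: improvement or persistence, with carried-forward values included. Then restate power, or the detectable difference, at the planned size, together with the cluster size used.

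The rate can be estimated from the baseline and look-back data before any intervention outcomes are examined, but only where patients have repeat values. The Baseline phase section enters these data where available and expects encounters to be irregular, so coverage may be thin. Otherwise give an explicit assumed range for the share at target and the persistence rate, and show power across it. If the prior-study 40% already counted persistence, correct the sentence to say so.

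Reassigning the 40%-to-50% calculation to the planned subgroup of patients not at target would not solve this. The article gives the 40% for diabetes patients in general. It would also call for 1153 patients in that subgroup alone, when the Setting section estimates about 1000 people with type-2 diabetes in the pilot communities.

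The cost is a recalculation and a few sentences. No change to treatment or data collection is needed. The stated power may become less favourable.
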